## Secondary endpoints

Secondary outcomes 2 to 7 below are time-to-event outcomes. For each, we will compute and plot the Kaplan-Meier estimates (outcomes 2, 4) or the competing risks Aalen-Johansen estimates (outcomes 3, 5, 6 and 7) and report the values of the estimates at 3, 6 and 12 months. We will also fit a Cox proportional hazards model (results are interpreted as relative cause-specific hazards in the presence of competing risks). Analyses will be performed for the full samples (ITT and PP). Subgroup analyses are specified below per secondary endpoint. For the subgroup analyses, we follow the same procedure as for the primary outcome: we fit separate models per subgroup and we fit a model in which we test for interaction by subgroup.

### 1. Neurological disability at 12 months from randomisation

Neurological disability will be assessed by the modified Rankin score at months 1, 2, 3, 6, 9, and 12 from randomisation (
Table 5). The main secondary endpoint is the 12-month assessment and subjects who died before 12 months will be treated as having a score of 6 (‘dead’). Rankin score assessments will be included from clinical assessments performed monthly (+/- 7 days), with the exception of the 12-month clinical assessment for which an acceptable range of -10 days/+1 month will be applied. All clinical assessment timings are based on days from randomisation (i.e., ‘day 0’ is labeled as the first day study drug is received, with study drug received immediately after randomisation).

**Table 5. T5:** The Modified Rankin Scale.

Score	Description
0	No symptoms
1	Minor symptoms not interfering with lifestyle
2	Symptoms that lead to some restriction in lifestyle, but do not interfere with the patients ability to look after themselves
3	Symptoms that restrict lifestyle and prevent totally independent living
4	Symptoms that clearly prevent independent living, although the patient does not need constant care and attention.
5	Totally dependent, requiring constant help day and night.
6	Death

Neurological disability (as assessed by the ordinal modified Rankin scale) at 12 months will be compared between the two arms with a proportional odds logistic regression model with the treatment assignment as the main covariate and adjustment for TBM MRC severity grade. The result will be summarised as a cumulative odds ratio with corresponding 95% confidence interval and p‐value. Individuals who withdrew or were lost to follow-up before 12 months are excluded.

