## Structure and status of trial

The ACT HIV trial commenced recruitment on 25
^th^ May 2017. By April 29
^th^ 2021, the predefined sample size of 520 adults with TBM and HIV co-infection had been enrolled from four hospitals in Vietnam and Indonesia: the Hospital for Tropical Diseases (HTD) and Pham Ngoc Thach Hospital for Tuberculosis and Lung Disease (PNT) in Ho Chi Minh City, Vietnam, and Cipto Mangunkusumo Hospital and Persahabatan Hospital in Jakarta, Indonesia. Detailed enrolment criteria for ACT HIV, including consent and ethical approvals, are described in the published trial protocol
^
1
^.

Once enrolled, study participants were randomised to dexamethasone or placebo (a double-blinded allocation), with this intervention termed ‘study drug’. Randomisation was stratified by TBM MRC severity score and by hospital. Participants with MRC grade 1 TBM received a 6-week tapering course of study drug, whereas participants with MRC grades 2 or 3 received an 8-week tapering course of study drug. Study drug regimens are shown in
Table 1. Participants then underwent clinical assessments at baseline, at days 3, 7, 10, 14, 21, and 30, monthly until month 12, and then 3-monthly until 24 months. Baseline assessment included blood tests, chest X-ray, lumbar puncture, and brain imaging.

**Table 1. T1:** Study drug treatment regimen following randomisation.

	MRC Grade I Daily dexamethasone dose/route	MRC Grades II and III Daily dexamethasone dose/route
Week 1	0.3 mg/kg/24 hrs IV	0.4 mg/kg/24 hrs IV
Week 2	0.2 mg/kg/24 hrs IV	0.3 mg/kg/24 hrs IV
Week 3	0.1 mg/kg/24 hrs IV	0.2 mg/kg/24 hrs IV
Week 4	3mg/24 hrs oral	0.1 mg/kg/24 hrs IV
Week 5	2mg/24 hrs oral	4 mg/24 hrs oral
Week 6	1 mg/24 hrs oral	3 mg/24 hrs oral
Week 7	Stop	2 mg/24 hrs oral
Week 8		1 mg/24 hrs oral

IV=intravenous. MRC=Modified Research Council.

ACT HIV has numerous sub-studies, as described in the protocol
^
1
^. Key follow up outcomes include survival, disability, and severe adverse events; especially neurological events, events requiring corticosteroids, HIV-associated complications (malignancies, immune reconstitution inflammatory syndrome [IRIS]), and adverse events considered related to dexamethasone.

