## Individuals included in analysis

### Primary analysis

The primary analysis includes all randomised participants. As such, an intention-to-treat (ITT) analysis will be performed for the primary and secondary endpoints. Participants will remain included in this analysis even if no study drug was received after randomisation.

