Anti-tuberculosis drug resistance ^ # ^ - Multi-drug resistant or rifampicin mono-resistant - Isoniazid resistant non-MDR - Pre-XDR - XDR - No or other resistance	XX XX XX XX XX	XX (XX%) XX (XX%) XX (XX%) XX (XX%) XX (XX%)	XX XX XX XX XX	X.XX X.XX X.XX X.XX X.XX	X.XX
ART status at enrolment - ART naïve - ≤3 months of ART - >3 months of ART	XX/XX XX/XX XX/XX	XX/XX XX/XX XX/XX	X.XX (X.XX, X.XX) X.XX (X.XX, X.XX) X.XX (X.XX, X.XX)	X.XX X.XX X.XX	X.XX
Enrolment CD4 count (per mm ^3^) - <50 - 51–100 - 101–200 - >200	XX/XX XX/XX XX/XX XX/XX	XX/XX XX/XX XX/XX XX/XX	X.XX (X.XX, X.XX) X.XX (X.XX, X.XX) X.XX (X.XX, X.XX) X.XX (X.XX, X.XX)	X.XX X.XX X.XX X.XX	X.XX

*Heterogeneity will be tested with a Cox regression model that includes an interaction between treatment effect and subgroup.
^#^Results will be given for sub-group with positive mycobacterial culture on baseline CSF. Pre-XDR and XDR are defined following World Health Organisation definitions
^
11
^. The primary endpoint will be overall survival, i.e., time from randomisation to death, over the first 12 months of follow-up. This table reports the results from the Cox proportional hazards regression model. The primary effect measure will be the resulting hazard ratio comparing dexamethasone vs. placebo with a corresponding two-sided 95% confidence interval. In these subgroup analyses, a separate Cox model will be fitted for each value of the subgroup. The "Test for heterogeneity" will be based on the likelihood ratio test that includes subgroup as covariate and compares the models with subgroup as main effect only and with subgroup as treatment effect modifier, with TBM MRC severity grade at enrolment (I, II, or III) as covariates. ART=antiretroviral therapy. MRC=Modified Research Council. TBM=tuberculous meningitis. XDR=extensively drug resistant.

Survivors known to be alive at 12 months will be censored at that time-point and subjects who withdrew or were lost to follow-up before 12 months will be censored at the date they were last known to be alive. Subjects who withdrew or were lost to follow-up before 12 months are estimated to be less than 5% of enrolled participants.

The homogeneity of the treatment effect on overall survival across subgroups will be assessed by formal tests of interaction between treatment and the following pre-defined grouping variables: TBM MRC severity grade at enrolment (I, II, or III), diagnostic category (definite, probable, possible),

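### The 12-month Rankin analysis excludes patients withdrawn or lost but scores deaths as 6, which conflicts with the all-randomised ITT set and tends to overstate the share scored 6

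*SAP article*

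**What the plan says.** Under Individuals included in analysis (Primary analysis), the SAP sets the population: "The primary analysis includes all randomised participants. As such, an intention-to-treat (ITT) analysis will be performed for the primary and secondary endpoints".

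Under secondary endpoint 1 (neurological disability) it gives three rules:
- The schedule: "Neurological disability will be assessed by the modified Rankin score at months 1, 2, 3, 6, 9, and 12 from randomisation". The 12-month assessment is the main one, with a window of -10 days/+1 month.
- Deaths: "subjects who died before 12 months will be treated as having a score of 6".
- Withdrawal and loss: "Individuals who withdrew or were lost to follow-up before 12 months are excluded".

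The comparison is a proportional odds model adjusted for MRC grade, summarised as a cumulative odds ratio.

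In the primary analysis the same patients stay in: "subjects who withdrew or were lost to follow-up before 12 months will be censored at the date they were last known to be alive". The SAP expects few of them: "Subjects who withdrew or were lost to follow-up before 12 months are estimated to be less than 5% of enrolled participants".

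**The concern.** Withdrawal and loss happen after randomisation, so removing these patients departs from the all-randomised set that the SAP announces for this endpoint.

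The removal is also one-sided. A recorded death always yields a score. A missing 12-month outcome arises only in someone who was alive when last seen, so the exclusion depends on the outcome scale itself. The proportion scored 6 tends to be too high, and the distribution of scores 0 to 5 rests on a selected group of survivors. If loss differs between the arms, part of that difference enters the cumulative odds ratio.

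The text also leaves two groups undefined:
- A patient who withdrew and is later known to have died before 12 months meets both the rule for deaths and the rule for exclusion.
- A patient still in follow-up with no score inside the 12-month window meets neither rule.

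**Working it through.** The SAP gives no figure for this rule, so there is none to reproduce. The check sizes the effect.

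**Inputs from the SAP**
- 520 enrolled (Structure and status of trial).
- Loss below 5% (Primary endpoint). 0.05 × 520 = 26, so strictly at most 25.

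**Assumptions, not in the SAP**
- 12-month mortality of 45%, with a range of 40% to 50%. The Background section puts mortality in this population near 50%.
- 260 per arm, since the allocation ratio is not stated.
- No true treatment effect.
- Survivors spread over scores 0 to 5 as 35/25/15/10/8/7%, with lost survivors spread the same way.
- No MRC adjustment.

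**Step 1: share scored 6, both arms together.** True deaths = 0.45 × 520 = 234. Let q be the fraction of the 25 lost patients who in fact died unobserved by 12 months. The analysed share is (234 − 25q) / 495.
- q = 0: 234/495 = 47.3%, against a true 234/520 = 45.0%.
- q = 0.25: 227.75/495 = 46.0%.
- q = 0.45: 222.75/495 = 45.0%, no distortion.
- q above 0.45: the sign reverses.

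With q = 0 the share becomes 42.0% at 40% mortality and 52.5% at 50%.

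There is a reason to expect q below the overall mortality. If loss is unrelated to prognosis, a patient lost at time t has already survived to t. The chance of death by 12 months is then 1 − S(12)/S(t), which is less than 1 − S(12). The upward tendency is therefore present even when censoring is independent.

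**Step 2: the planned treatment comparison.** I fitted the proportional odds model to expected counts, with a true odds ratio of 1.00 and all lost patients alive (q = 0).

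| Lost, arm A vs arm B | Cumulative OR (worse score), B vs A, 40% to 50% mortality |
|---|---|
| 12.5 vs 12.5 | 1.00 |
| 9 vs 16 | 1.04 to 1.05 |
| 7.8 vs 18.2 (3% vs 7%) | 1.06 to 1.08 |
| 5 vs 20 | 1.09 to 1.12 |

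The 3% versus 7% row adds to 26 patients, just over the strict bound.

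At 45% mortality that row gives 1.070, or 1/1.070 = 0.93 to 0.94 the other way round. The standard error of the log odds ratio is about 0.166, so the shift is ln(1.070)/0.166 = 0.068/0.166 ≈ 0.4 standard errors. If a quarter of the lost had died unobserved, the odds ratio is 1.03 (inverse 0.97).

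A hand check at the death cut alone for 3% versus 7%: 0.45/0.97 = 46.4% and 0.45/0.93 = 48.4%. The odds ratio is (0.464/0.536)/(0.484/0.516) = 0.92, slightly further from 1 than the common odds ratio that the SAP will report.

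**The case against.** The best defence is that the ITT statement defines the population, while the Rankin section says how missing outcomes are handled. Nobody is moved between arms or removed for non-adherence, and the rule is disclosed in advance. On that view, calling it a complete-case analysis of the ITT set repairs the text. Loss is expected below 5%, allocation is double-blind, and nothing in the SAP points to unequal loss. This is a secondary endpoint, and the primary analysis keeps these patients by censoring.

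Most of this stands, and it limits the size of the point. A relabel would remove the contradiction in wording. It would not remove the dependence of the exclusion on the outcome, nor settle the two undefined groups.

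The objection that the shift assumes every lost patient is alive at 12 months is also fair: 47.3% is the figure for that case. Being alive at last contact does not establish being alive at 12 months.

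Three stronger readings are not supported:
- That the SAP breaks its own imputation rule. That rule stands under Baseline characteristics and applies above 5% missing. At the expected loss it would itself lead to a complete-case analysis.
- That the earlier Rankin scores go unused. They do not enter the 12-month model, but the SAP does not say that they will go unreported.
- That raising the share scored 6 in itself biases the treatment comparison. With equal loss and no true effect, the odds ratio stays at about 1.00.

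**Conclusion.** The point holds, with modest size. The all-randomised statement and the Rankin exclusion conflict as written, and the exclusion removes only patients who were alive when last seen.

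The overall share scored 6 is overstated by up to about 2.3 percentage points (47.3% against 45.0%). This assumes 45% mortality, 25 lost and all of them alive at 12 months. Unobserved deaths would reduce the excess, and could reverse it if they exceeded the cohort rate.

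The treatment comparison is at risk mainly from unequal loss. The 3% versus 7% split is an illustration that the SAP does not suggest. A reader might infer from the exclusion that the Rankin result will be materially biased. At the expected level of loss the SAP does not support that.

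The change is still worth making: the rule leaves analyst discretion over who enters the model, and a better method is available from data already scheduled.

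**What to change.** 1. Analyse all randomised participants with the same MRC-adjusted proportional odds model. Multiply impute the missing 12-month score from arm, MRC grade, age, enrolment GCS and the available month 1 to 9 Rankin scores.
2. Restrict the imputed score to 0 to 5 for anyone known to be alive at 12 months, including survivors with no score inside the -10 days/+1 month window. For those whose vital status is unknown, allow 0 to 6.
3. State that a withdrawn patient known to have died before 12 months is scored 6.
4. Keep the exclusion analysis as a sensitivity analysis, labelled complete-case.
5. Report the number without a 12-month score by arm, with a best-case and worst-case check.

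The cost is a few sentences in the SAP and one imputation model, with no new data collection. The imputation assumes data missing at random given the earlier scores. Patients lost very early may have no earlier score to draw on, so the best/worst-case check should accompany it.

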### 2. First new neurological event or death over the first 12 months after randomisation

A new neurological event is defined as a fall in GCS by ≥2 points for ≥2 days from the highest previously recorded GCS (including baseline) or the onset of any of the following clinical adverse events: cerebellar symptoms, focal neurological signs, or onset of seizures. A description of all the events will be given, summarising how they met the criteria.

Analyses will additionally be performed in the subgroups defined by TBM MRC severity grade, diagnostic category, ART status at enrolment, time from randomisation to start of ART, and baseline CD4 count.

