## Background and rationale for study

The ACT HIV clinical trial is a randomised double-blind placebo-controlled trial of adjunctive dexamethasone for the treatment of tuberculous meningitis (TBM) in HIV-positive adults. TBM is the most severe form of tuberculosis, with mortality approaching 50% in people living with HIV
^
2–
5
^ despite the best available appropriate anti-TB chemotherapy.

TBM develops when
*Mycobacterium tuberculosis*, initially acquired via the respiratory route, disseminates via the blood to form a secondary focus in the brain. Rupture of this secondary focus into the subarachnoid space results in TBM, with the consequent host inflammatory response being important for bacterial killing, but also responsible for the pathological complications and often-fatal consequences of the infection.

Adjunctive anti-inflammatory corticosteroid therapy, which may control excessive host inflammation, has long been considered to have a role in TBM treatment
^
6
^. In 2004, a landmark clinical trial in Vietnam demonstrated that a 6–8 week (duration dependent on Modified Research Council [MRC] TBM severity grade) tapering course of dexamethasone reduced mortality in adults and adolescents with TBM
^
4
^. In this study, only 98/545 (18.0%) individuals were HIV positive, which was too small to determine if dexamethasone benefited this important sub-group of patients. No other trials have been published since 2004 that examine whether corticosteroids improve outcomes from TBM in HIV-positive adults.

How dexamethasone might confer its clinical benefit on those with TBM remains uncertain. A recent study of cerebrospinal fluid (CSF) cytokines in TBM suggested that HIV-positive individuals have higher cytokine concentrations than HIV-negative individuals
^
7
^. Whether adjunctive dexamethasone is more or less likely to be beneficial in HIV-positive individuals with TBM is not known. There are an estimated 100,000 cases of TBM globally each year
^
8
^, many associated with HIV. Clinical trial data are required to provide an evidence base for adjunctive dexamethasone in HIV-positive individuals with TBM, and to guide clinical practice.

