## Baseline characteristics

Definition: The following baseline characteristics will be summarised by treatment arm for ITT and PP analyses: age, sex, country, site, diagnostic category (definite, probable, possible, or not TBM by Marais criteria
^
10
^), history of previous tuberculosis treatment, chest X-ray findings (no TB/miliary TB/pulmonary TB), enrolment MRC TBM grade, enrolment Glasgow coma score (GCS), weight (kg), duration of symptoms, cranial nerve palsy, hemiplegia, para/tetraplegia, urinary retention, history of diabetes, HbA1c, history of intravenous drug use, hepatitis B sAg positivity, hepatitis C Ab positivity, alanine aminotransferase (ALT), bilirubin, full blood count (haemoglobin, white cell count, platelets), plasma sodium,
*leukotriene A4 hydrolase* (
*LTA4H*) genotype (CC/CT/TT), routine CSF parameters (opening pressure, total leucocytes, total neutrophils, total lymphocytes, protein, blood:CSF glucose ratio, Ziehl-Neelsen stain, Gene Xpert MTB/RIF, Gene Xpert MTB/RIF Ultra, mycobacterial culture), duration of anti-tuberculosis chemotherapy (days) before enrolment, enrolment anti-TB regimen, anti-TB drug susceptibility results in culture-confirmed sub-group (multi-drug resistant [MDR] TB or rifampicin mono-resistant TB, isoniazid resistant non-MDR, pre-extensively drug resistant [XDR] TB, XDR TB, no or other resistance), HIV infection (new or known diagnosis), anti-retroviral therapy (ART) treatment at enrolment (ART naïve, ≤3 months of ART, >3 months of ART) and time to starting ART (if ART naïve), enrolment CD4 count (median values and categories [<50, 51–100, 101–200, >200]), HIV viral load. These will be described in a baseline variable table (
Table 2).

**Table 2. T2:** Baseline characteristics template table.

Characteristic	Dexamethasone (N=XX)		Placebo (N=XX)	
	N	Summary statistic	N	Summary statistic
Age (years)	XX	XX (XX,XX)	XX	XX (XX,XX)
Sex - male	XX	XX (XX%)	XX	XX (XX%)
Country	XX	XX (XX%)	XX	XX (XX%)
Site - HTD - PNT - Cipto Mangunkusumo - Persahabatan	XX XX XX XX	XX (XX%) XX (XX%) XX (XX%) XX (XX%)	XX XX XX XX	XX (XX%) XX (XX%) XX (XX%) XX (XX%)
Diagnostic category - Definite TBM - Probable TBM - Possible TBM - Not TBM	XX XX XX XX	XX (XX%) XX (XX%) XX (XX%) XX (XX%)	XX XX XX XX	XX (XX%) XX (XX%) XX (XX%) XX (XX%)
Previous tuberculosis treatment	XX	XX (XX%)	XX	XX (XX%)

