### 3. First IRIS event over the first 6 months after randomisation

The criteria for neurological IRIS diagnosis is defined in the study protocol
^
1
^. The neurological IRIS rate will be defined as the number of IRIS events divided by the observed person-time of follow-up in each treatment group. A description of all the IRIS events will be given, describing how they met the IRIS diagnostic criteria.

The number of IRIS events in each group will be summarised. Death will be interpreted as a competing risk. Analyses will additionally be performed in the subgroups defined by TBM MRC grade, diagnostic category, ART status at enrolment, time from randomisation to start of ART, and baseline CD4 count.

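### Secondary outcomes 2 and 3 use time from randomisation to start of ART as if it were a baseline subgroup; treatment hazard ratios within those groups, and the interaction test, can be biased

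*SAP article*

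**What the plan says.** The SAP section on secondary endpoint 2 (new neurological event or death, 12 months) asks for analyses in "subgroups defined by TBM MRC severity grade, diagnostic category, ART status at enrolment, time from randomisation to start of ART" and baseline CD4 count. The section on secondary endpoint 3 (IRIS, six months, death as a competing risk) asks for them in "subgroups defined by TBM MRC grade, diagnostic category, ART status at enrolment, time from randomisation to start of ART" and baseline CD4 count.

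The opening paragraph of the Secondary endpoints section fixes the method, the same as for the primary outcome: "we fit separate models per subgroup and we fit a model in which we test for interaction by subgroup". Follow-up starts at randomisation. That paragraph and the two endpoint sections state no landmark, delayed entry or time-dependent covariate for ART start.

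The primary-endpoint subgroups are different. There ART enters only as status at enrolment, and time to ART is not on the list.

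**The concern.** The other variables in the two lists describe the patient's state or disease at enrolment. Time to ART does not. It is observed only in patients who live long enough to start, and the course of the illness after randomisation may influence it. The Background section expects "mortality approaching 50% in people living with HIV", so deaths before ART need not be few.

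Two things follow by construction. A patient who starts ART at eight weeks cannot have died in weeks one to eight, so a group starting after eight weeks contains no deaths from the period in which study drug is given (six or eight weeks, by MRC grade). A patient who dies before ART has no start time and so fits no start-time group.

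Randomisation balances the arms at entry. It does not guarantee balance among patients selected on something that happens later. What is at stake is a published statement that dexamethasone works differently according to when ART is started, when the pattern may only reflect who survived to be classified.

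**Working it through.** The SAP gives no figure on this point to reproduce. The calculation below only illustrates when the problem appears and how large it can be.

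**Assumptions, none fixed by the SAP.** Death stands in for the actual endpoints. Twelve-month mortality is 45%, compared with the SAP's approximate 50%. The hazard is front-loaded (Weibull, shape 0.5). Planned ART start is uniform from 0.5 to 3 months, unrelated to prognosis, and happens only if the patient is alive. Start groups are up to 1 month, 1–2 months and 2–3 months.

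**Step 1: selection by survival.** The cumulative hazard is H(t) = −ln(0.55) × √(t/12) = 0.598 × √(t/12), with t in months. At the group midpoints H(0.75) = 0.149, H(1.5) = 0.211 and H(2.5) = 0.273; also H(2) = 0.244. Mortality by month 12 among patients alive to start at s is 1 − exp{−[0.598 − H(s)]}:

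- s = 0.75: 1 − exp(−0.448) = 36%
- s = 1.5: 1 − exp(−0.387) = 32%
- s = 2.5: 1 − exp(−0.325) = 28%

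All three groups would have 45% if classified by planned start. About 20% of patients die before starting. This is with no treatment effect and no effect of ART.

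**Step 2: treatment effect confined to the first two months (HR 0.70, then 1).** The ratio of cumulative hazards from ART start s (before month 2) to month 12 is [0.70 × (H(2) − H(s)) + (0.598 − H(2))] / [0.598 − H(s)]:

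- all patients, s = 0: (0.70 × 0.244 + 0.354)/0.598 = 0.88
- s = 0.75: (0.70 × 0.095 + 0.354)/0.448 = 0.94
- s = 1.5: (0.70 × 0.033 + 0.354)/0.387 = 0.97
- s = 2.5: 1.00, because nothing of the effect period is left

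**Step 3: Cox HRs by simulation under the same design.** Frailty here means unmeasured risk, gamma with variance 1. Repeated runs agree to about 0.01.

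| True effect | Frailty | Overall | Start up to 1 month | 1–2 months | 2–3 months |
|---|---|---|---|---|---|
| None | no | 1.00 | 1.00–1.01 | 1.00–1.01 | 1.00–1.01 |
| HR 0.70 throughout | no | 0.70 | 0.70 | 0.70 | 0.70 |
| HR 0.70 throughout | yes | 0.76 | 0.77–0.79 | 0.77–0.79 | 0.77–0.79 |
| HR 0.70 in months 0–2 only | no | 0.86 | 0.93 | 0.97 | 1.01 |
| HR 0.70 in months 0–2 only | yes | 0.88 | 0.98 | 1.04 | 1.07 |

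**Step 4: a second set of assumptions.** With 50% mortality, 60% of the cumulative hazard in days 0–60, ART planned for days 14–84 and groups cut at days 28 and 56, an HR of 0.69 limited to days 0–60 gives 0.80 overall and 0.83, 0.89 and 1.01 by start group. About 26% die before ART when treatment has no effect. If the drug has no effect on death, but sicker placebo patients start ART 21 days later while sicker dexamethasone patients do not, the overall HR is 1.00 and the groups show 1.97, 1.14 and 0.87.

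**The case against.** The strongest reply is that the SAP asks for treatment contrasts within groups, and survival selection alone does not bias those. This stands. With no effect on death or ART timing, the arms remain comparable and the HRs stay near 1. With a constant HR and no unmeasured risk, they stay at about 0.70. A reader might infer that the HRs are biased in every case; the calculation does not support that.

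Other limits also stand:

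- The mortality gradient in step 1 arises with no treatment effect. It shows that start groups cannot be compared with each other. It does not show a biased treatment HR.
- The benefit disappears from all three groups only when an early-only effect is combined with strong frailty. Without frailty the earliest group still shows 0.93. A value near 1 in late starters is then correct for the time they are actually at risk; the error is reading it as effect modification by ART timing.
- The simulations use death alone. A non-fatal neurological event does not bar a patient from starting ART, though it may delay it. No size is available for the composite or for IRIS, whose criteria are in the protocol.
- Nothing in the SAP shows that study drug changes when ART is started. The drug is double-blind and any ART-start rules lie outside this document. The last scenario in step 4 is a possibility only.
- Time to starting ART also appears in the baseline table. That is a descriptive summary in ART-naïve patients and a matter of presentation; it is not part of this point.

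These limits reduce the size and certainty of the bias. They do not rescue the rule. The conditions for a sound HR cannot be assumed in advance, because whether the drug changes survival is what the trial tests, and the drug is given for only six to eight weeks.

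**Conclusion.** The point holds in conditional form. The SAP specifies a subgroup variable that is post-randomisation and depends on survival, with a model suited to baseline variables. The resulting HRs and interaction test can be biased if the drug changes early survival or ART timing, or if unmeasured risk is present. They are essentially unbiased if the drug affects neither, or if the HR is constant with no unmeasured risk.

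Under the first set of assumptions the distortion ranges from none (constant HR, no frailty), through 0.77–0.79 against 0.76, to 0.98, 1.04 and 1.07 against 0.88. These sizes rest on assumed hazards and ART timing, with death as the only event.

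Severity is moderate. The defect concerns one subgroup variable in two of the eight secondary endpoints. A reader might infer that the trial's main result is at risk. It is not: the primary analysis, its subgroups, the full-sample secondary analyses and the other subgroup variables are unaffected.

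**What to change.** Remove time from randomisation to start of ART from the subgroup lists of secondary endpoints 2 and 3, and keep ART status at enrolment.

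If ART timing is of interest, use one of two analyses, labelled non-randomised and exploratory:

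- ART start as a time-dependent covariate, with an interaction with treatment arm; or
- a landmark analysis among patients alive and event-free at a fixed day, grouped by ART status at that day. It should be stated that this cannot show effects before the landmark.

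For either, state in advance the landmark day or timing categories, and how patients already on ART at enrolment and those who never start are handled. The cost is SAP wording and a little programming; the same dates are used and no further data are needed.
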